## Abstract

**Background:**

People with physical disabilities need exercise routines that are enjoyable, readily available in the home, adapted to their functional level, and eliminate common barriers to exercise participation related to transportation and time commitment. The purpose of the movement-to-music (M2M) study is to address these issues by establishing a remotely delivered, rhythmic exercise program for people with physical disabilities.

**Methods:**

The study is a two-arm randomized controlled efficacy trial examining a 12-week remotely delivered M2M intervention (eM2M) in 108 people with physical disabilities. The primary outcomes are changes in cardiorespiratory fitness and muscle strength at post 12-week intervention.

**Discussion:**

The eM2M study will enhance our understanding of an alternative intervention design and delivery mode that removes common barriers to exercise participation experienced by people with physical disabilities. The eM2M intervention may be an alternative option for people with physical disabilities to obtain regular exercise, especially during a pandemic when exercising in indoor facilities may be problematic.

**Trial registration:**

ClinicalTrials.gov NCT03797378. Registered on January 9, 2019, with the trial name “Movement-to-Music: Lakeshore Examination of Activity, Disability, and Exercise Response Study (M2M LEADERS)”.

## Administrative information

Note: the numbers in curly brackets in this protocol refer to SPIRIT checklist item numbers. The order of the items has been modified to group similar items (see http://www.equator-network.org/reporting-guidelines/spirit-2013-statement-defining-standard-protocol-items-for-clinical-trials/).

## Introduction

### Background and rationale {6a}

Exercise trials for people with physical disabilities are currently challenged by the inability to reach large, heterogenous groups of participants that are representative of the target population. Studies typically incorporate highly controlled designs and focus on examining one specific disability group in an exercise intervention with an average sample size of 40 participants per study [1, 2]. Because of this, the generalizability and transferability of the research is limited, which creates a need to identify evidence-based exercise interventions that are robust enough to be successfully used by multiple disability groups [3]. To address this limitation, one potential strategy is for studies to include people within the exercise intervention based upon their physical function, as opposed to a specific type of disability.

Creating exercise interventions for different levels of physical function present a few challenges. For example, when an exercise intervention is delivered to participants with various levels of functional mobility, people with higher or lower levels of physical function may perceive the program as not challenging or too difficult, which may compromise the physiological adaptations achieved from the intervention. Froehlich-Grobe et al. examined the effectiveness of a physical activity intervention for women with a wide variety of mobility limitations and reported no significant physiologic change [4]. They suggested that a possible reason for this nonsignificant finding was the variability in functional mobility levels. The authors recommended that in future studies, researchers should design exercise interventions using a functionally based approach to ensure that every participant receives a similar exercise stimulus.

In addition to addressing the physiologic training needs in people with physical disabilities, it is also important to ensure that the interventions are accessible. Common barriers to exercise experienced by people with physical disabilities include lack of transportation to and from exercise venues, cost of the program, inaccessible fitness facilities, and time constraints [5]. Fortunately, there are a growing number of scalable telehealth technologies that have the potential to reach large numbers of people with disabilities in the comfort of their home [6]. In a recent review, we found that technology-driven exercise intervention studies sustained 56% of all outcomes measured at follow-up, compared to 24% for the exercise intervention studies that used technology only for measurement purposes [7]. Given the low rate of exercise participation among people with physical disabilities [8], there is a pressing need to continue exploring the potential of using telehealth technologies to deliver home-based exercise, or what we refer to as teleexercise, among people with disabilities.

Providing exercise that is enjoyable is also important as it will likely increase adherence to the exercise program in people with physical disabilities. Many fitness-related training protocols such as treadmill walking, stationary cycling, and weight lifting often have low adherence rates due to lack of enjoyment or social interaction [9–11]. Asano et al. surveyed 417 people with multiple sclerosis and found “dislike exercise” and “find exercise boring” were common reasons for not exercising [12]. Providing alternative and enjoyable forms of exercise thus becomes critical in helping individuals find activities that fit their interests and needs. Several studies have reported that music is an effective strategy for improving exercise adherence [13–16] and enjoyment [17, 18]. Listening to music during exercise is associated with positive moods and feelings [19]. Indeed, evidence suggests that dance is a promising intervention for improving physical function in people with Parkinson’s [20, 21], stroke [22], and other disabling conditions [23–25]. An additional benefit is that movement-based exercise with music can be performed almost anywhere with minimal equipment.

### Objectives {7}

The movement-to-music (M2M) study aims to examine a rhythmic-based teleexercise intervention (eM2M) with 108 adults with physical disabilities. Specifically, the **primary aim** is to investigate effects of the 12-week eM2M intervention on physical and psychosocial health outcomes in participants who are classified into three functional mobility groups: Group I—only able to exercise while sitting, Group II—able to exercise sitting and standing with or without support, and Group III—able to exercise one side of the body more than the other side. We hypothesize that participants who receive the 12-week eM2M intervention will have the following:
Significantly higher gains in cardiorespiratory fitness and muscle strength compared to waitlist control (*WC*) participants post-intervention.Significantly greater gains in lower extremity function, physical activity, health-related quality of life, and social participation compared to *WC* participants post-intervention.

The **secondary aim** is to compare the effect sizes of eM2M on physical health outcomes including cardiorespiratory fitness, muscle strength, and lower extremity function with those observed in a previous M2M trial [26] that grouped participants based on disability type. We hypothesize that gains in physical health will be larger than in the previous M2M trial where participants were grouped by disability type.

The **tertiary aim** is to explore the role of group cohesion, instructor support, exercise self-efficacy, exercise self-regulation, social support for exercise, and outcome expectations for exercise as mediating variables between eM2M and the primary and secondary outcomes. The heterogeneity of treatment effect across the physical health outcomes will also be examined using functional mobility and disability type as moderators.

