### Sample size {14}

Our conservative sample size and power calculations for the primary outcomes, which constitute a family of hypotheses [63], assume a two-sided overall family-wise error rate of 0.05 [64], 80% power, an analysis of covariance (ANCOVA)-based approach, and an attrition rate of 25% with 82 participants finishing the study. Under these assumptions, we will have 80% power to detect at least a minimally detectable difference (Cohen’s *d*) of 0.552. In these calculations, a conservative correlation of 0.6 between the baseline covariate and outcome is assumed, which is similar to a previous study by Froehlich-Grobe et al. [4].

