## Statistical methods

### Statistical methods for primary and secondary outcomes {20a}

#### Primary analysis

The primary analysis for the average treatment effect (**primary aim**) will employ an intent-to-treat linear mixed model ANCOVA with the baseline outcome measures as covariates, the corresponding post-intervention outcome measures as the dependent variables, the intervention as the main factor, and the intervention waves as random effect. In general, missingness will be handled by our choice of mixed models to handle the multi-level data. Mixed models use all the data available to directly estimate model parameters via maximum likelihood or restricted maximum likelihood. Where necessary, we will supplement these primary analyses by using multiple imputation procedures with 10 imputations [4]. We have configured three families of hypotheses based on our primary and secondary outcomes.

For the **secondary aim**, we will estimate the effect sizes and their 95% confidence intervals and compare them with the corresponding effect sizes and interval estimates from a previous M2M trial [65]. We will generate 95% percentile bootstrap confidence intervals between the differences in the effect sizes utilizing data from both trials. To test for pre-specified moderators, we will extend our models in the primary aim to include moderators as main effects along with an interaction term with the intervention. A test for interaction between the moderator and intervention will be conducted.

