## Discussion

Nearly one out of two people with disabilities (46%) in the USA is categorized as physically inactive [69]. In a 2014 Centers for Disease Control and Prevention report [70], less than 10% of people with physical disabilities performed aerobic exercise, one of the key markers for optimal health and prevention of chronic disease. The report noted that sedentary people with disabilities were three times more likely to report primary health conditions such as heart disease, stroke, diabetes, or cancer compared to active people with disabilities. People with disabilities need immediate resources that they can use to obtain regular exercise.

Being aware of the multiple barriers that many people with disabilities experience when trying to become physically active, there are important questions that this study will address. First, there are very few non-conventional exercise options for people with disabilities. The current study will examine a novel rhythmic exercise intervention that utilizes music to facilitate exercise and will provide evidence on efficacy of this alternative exercise programming. Second, the *e*M2M intervention is designed to include participants with different disabilities and similar functional mobility in a group class setting. The study will test whether a greater intervention effect can be obtained with participants with a more homogeneous range of physical function and will enhance our undestanding of effective design strategies of a home-based exercise intervention for people with disabilities. Third, many people with physical disabilities have difficulty getting to an exercise facility on a regular basis. This is due to factors including but not limited to long delays for transportation services and inaccessible exercise facilities. The M2M study is designed to be delivered completely online so that participants can complete the assessments and intervention in the comfort of their own home. Thus, the study will provide detailed documentation of such an intervention delivery mechanism and will be helpful for designing future studies involving people with disabilities.

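### The Discussion says the trial will test functional grouping, but grouping is compared only across two separate trials, so no difference found can be attributed to it

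*Protocol article*

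**What the plan says.** Objectives {7} sets the secondary aim: compare the effect sizes of eM2M on cardiorespiratory fitness, muscle strength and lower extremity function with those of a previous M2M trial whose participants were grouped by disability. It adds a direction: "We hypothesize that gains in physical health will be larger than in the previous M2M trial where participants were grouped by disability type".

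The Discussion lists the question among those the study will address: "The study will test whether a greater intervention effect can be obtained with participants with a more homogeneous range of physical function".

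The analysis is in the section Primary analysis under Statistical methods {20a}. Effect sizes with 95% confidence intervals will be set beside those of the earlier trial, and then: "We will generate 95% percentile bootstrap confidence intervals between the differences in the effect sizes utilizing data from both trials". That section does not state the scale of the effect size, any adjustment for differences between the trials, or any limit on interpretation.

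Trial design {8} has two arms, eM2M and waitlist control. Intervention description {11a} provides three programmes defined by functional mobility, and the adherence section {11c} confirms that classes bring together people of similar functional level. Sample size {14} concerns the primary outcomes only. It is the one place where an effect-size metric is named: "minimally detectable difference (Cohen’s *d*) of 0.552".

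**The concern.** A claim to test a grouping strategy needs a contrast in which grouping varies and other things are comparable. Within this trial grouping does not vary: no participant is grouped by disability type. The contrast exists only between this trial and one already completed, and randomization within each trial does not carry over to it.

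The planned interval will have the form of a formal comparison of two strategies. If it lies above zero, it invites the conclusion that functional grouping works better. If it covers zero, it invites the conclusion that grouping makes no difference. The design supports neither. This matters because grouping by function is the main design idea of the Background, and later studies may be built on the answer.

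**Working it through.** **1. What the cross-trial difference contains.** Let D1 be the effect here (functional grouping, this trial's conditions) and D2 the effect in the earlier trial (disability grouping, that trial's conditions). Assume D2 is also a contrast with a control; the documents do not say. Then

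D1 − D2 = (effect of grouping) + (effect of every other difference between the trials).

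There is one estimable quantity and there are two unknown terms. Resampling participants within each trial gives an interval for the sum and does not separate the terms. For this trial the documents give the second term's ingredients: remote delivery, remote assessment, seven eligible diagnoses, and recruitment from December 2020 to an expected end in July 2022. For the earlier trial they give only that it was an M2M trial grouped by disability type.

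**2. Whether the moderator tests fill the gap.** They do not. Interactions of the intervention with functional mobility and with disability type ask whether the eM2M effect differs between kinds of participant. They do not ask whether it differs with how classes are composed.

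**3. The plan's own figure.** Inputs from Sample size {14}: 82 completers (41 per arm, taking the allocation as 1:1), baseline–outcome correlation 0.6, 80% power, family-wise 0.05. Splitting 0.05 over the two primary domains gives 0.025 each:

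d = (2.241 + 0.842) × √(1 − 0.6²) × √(2/41) = 3.083 × 0.8 × 0.2209 = 0.545.

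The noncentral t version gives 0.554. The stated 0.552 is reproduced and is not in question.

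**4. Scale, if each trial's own SD is the divisor (assumption).** For the same raw gain, d is proportional to 1/SD. An SD 20% smaller gives 1/0.8 = 1.25, that is, a d 25% larger. Take a raw gain worth 0.552 in the earlier trial:

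| SD here / SD earlier | d here | Spurious difference |
|---|---|---|
| 0.7 | 0.79 | +0.24 |
| 0.8 | 0.69 | +0.14 |
| 1.0 | 0.55 | 0 |
| 1.25 | 0.44 | −0.11 |
| 1.5 | 0.37 | −0.18 |

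The planned bootstrap was simulated with equal raw effects: unadjusted normal data, 41 per arm in both trials, 1,000 simulated pairs of trials, 500 resamples each. The 95% interval lay wholly above zero in 2.3% of runs at SD ratio 1.0, 6.5% at 0.8 and 11.8% at 0.7. The ratios are hypothetical, because the documents give no SDs for either trial.

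**5. Precision (illustrative).** SE(d) here = √(0.64 × 2/41) = 0.177. The cross-trial difference detectable with 80% power is

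- 2.80 × 0.177 = 0.50 if the earlier effect were known exactly;
- 0.50 × √2 = 0.70 if the earlier trial were equally precise (assumption).

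With ANCOVA precision, the 95% half-width is 1.96 × 0.8 × √(4/82 + 4/N), where N is the earlier trial's total. It is 0.61 for N = 40, 0.49 for N = 82 and 0.41 for N = 200. The earlier N is not given.

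**The case against.** A difference between two trials is a legitimate thing to estimate, and it may carry a stated hypothesis. The Objectives sentence literally predicts larger gains than in another trial and identifies that trial by how it grouped people. The analysis section only estimates and compares. This stands: the hypothesis need not be deleted, and the explicit attribution is in the Discussion sentence. It does not rescue that sentence, which claims a test of homogeneity of function without any caveat.

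A reader might infer that grouping is known to be confounded with delivery mode, diagnoses or method of measurement. The documents do not support that, because they describe none of these for the earlier trial. They are examples of what could differ. The point needs only the absence of a concurrent, randomized disability-grouped arm.

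A reader might also infer that the comparison is distorted by unequal SDs as a matter of fact. The analysis section says only effect sizes, Cohen's d is named only for the sample size, and having both datasets leaves original units or a common SD open. The scale point is therefore conditional. Nor does grouping imply a smaller SD here: homogeneity within a class is not homogeneity of the whole trial, which pools all three functional groups.

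Finally, the magnitude is moderate. A shift of 0.14 is small beside a half-width of about 0.49, and the plan claims no power for this aim.

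A statistical analysis plan could settle the scale and the covariates. It could not supply the missing arm.

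**Conclusion.** The point holds in this form: the Discussion credits the trial with a test that its design does not contain, and the secondary aim's interval, whatever it shows, cannot be attributed to functional grouping. That conclusion rests on the documents alone and needs no assumption about the earlier trial beyond its being separate and earlier.

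The scale problem is an added risk only if each trial's own SD is the divisor. Its direction cannot be determined, and its size depends on an unknown SD ratio (25% inflation of d at a ratio of 0.8). The detectable difference of 0.50 to 0.70 shows that the comparison would also be imprecise, but it contradicts nothing in the plan.

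The sample-size figure and the randomized comparison of eM2M with waitlist control are unaffected. The change should be made because it alters what the trial may conclude and costs little.

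**What to change.** 1. In Objectives {7} and in Primary analysis, label the secondary aim a non-randomized, descriptive cross-trial comparison, and state that a difference cannot be attributed to functional grouping. The directional expectation may stay with that limit beside it.
2. In the Discussion, replace the wording that the study will test the effect of homogeneous function with wording that matches: the effects will be described alongside those of an earlier trial.
3. In Primary analysis, fix the scale. Use baseline-adjusted mean differences in original units, or one common baseline SD for both trials, for measures taken in both. The bootstrap interval can be kept on that scale.
4. While editing, reconcile the comparator's citation. The earlier trial is reference 26 in Objectives {7} and 65 in Primary analysis, while Secondary analysis uses 26 for the mediation method.

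The cost is wording plus a choice of scale in data the plan already intends to use. The downside is a weaker claim. Restricting or weighting by diagnosis is optional and depends on what the earlier dataset holds.

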### Trial design {8}

The M2M study is a two-arm randomized controlled efficacy trial. Eligible and enrolled participants will be randomized into one of two study arms: *eM2M* and *WC*. The overall study structure is illustrated in Fig. 1.

**Fig. 1 Fig1:**
[figure not shown]
Overall M2M study structure

## Methods: participants, interventions, and outcomes

### Study setting {9}

The entire study will be conducted remotely through a telehealth facility located at the study site. All physical outcomes will be assessed via a HIPAA-protected Zoom videoconferencing platform (teleassessments). All self-report outcomes will be collected using electronic surveys delivered through the Research Electronic Data Capture (REDCap). The eM2M intervention will be delivered through the same Zoom platform, which is connected to a custom built, password-protected intervention website housed within an encrypted server at the university. The website will be used to collect vital signs and physical condition questions before and after each eM2M session.

### Eligibility criteria [27]

Individuals are eligible to participate in the study after meeting all inclusion criteria, which include (1) primary diagnosis of traumatic brain injury, stroke, multiple sclerosis, spinal cord injury, spina bifida, Parkinson’s disease, or cerebral palsy conferred by a physician; (2) fits one of the three functional mobility groups: Groups I–III; (3) between the ages of 18 and 70 years; (4) physician clearance to participate; (5) willing to participate in an exercise program 3 times per week; (6) conversant in and reads English; (7) have internet access. The exclusion criteria are (1) participated in a short-term rehabilitation program or a similar intervention in the last 6 months; (2) use of tobacco products in the last 6 months; (3) score <19 on the Telephone Interview for Cognitive Status [27]; (4) active pressure ulcer; (5) any contraindications to exercise based on the American College of Sports Medicine (ACSM) guidelines [28]; (6) visual acuity that prevents following a group exercise class; (7) significant hearing impairment impeding ability to hear music to engage in exercise; and (8) currently pregnant.

### Who will take informed consent? {26a}

Upon completion of the screening process with a study recruitment coordinator, eligible individuals will receive an electronic consent form via REDCap and will officially enroll in the study after signing the informed consent form.

### Additional consent provisions for the collection and use of participant data and biological specimens {26b}

This study does not involve collecting biological specimens for storage. The consent form asks if participants are willing to be contacted for future research opportunities. Participants can decline to this option and still participate in the M2M study.

### Interventions

Enrolled participants who complete baseline assessments will be randomly assigned to *eM2M* or *WC*. After randomization, participants in the *eM2M* arm will meet virtually with study staff who will provide information about the intervention schedule and an online program (e-STORIES) [29] on exercise self-regulation strategies, including goal setting, to be completed prior to beginning the intervention. Participants in *WC* will be instructed to maintain their usual activities during the 12-week intervention and will be invited to participate in an eM2M program after the control period. Both *eM2M* and *WC* participants will be asked to complete a weekly electronic survey on their physical activity level.

